## Abstract

**Background:**

Premature infants commonly encounter difficulties with oral feeding, a complication that extends hospital stays, affects infants’ quality of life, and imposes substantial burdens on families and society. Enhancing preterm infants’ oral feeding skills and facilitating their transition from parenteral or nasal feeding to full oral feeding pose challenges for neonatal intensive care unit (NICU) healthcare professionals. Research indicates that oral motor interventions (OMIs) can enhance preterm infants’ oral feeding capabilities and expedite the transition from feeding initiation to full oral feeding. Nonetheless, the most suitable timing for commencing these interventions remains uncertain.

**Methods:**

This is a single-blind, randomized controlled trial. Preterm with a gestational age between 29^+0^ to 34^+6^ weeks will be eligible for the study. These infants will be randomized and allocated to one of two groups, both of which will receive the OMIs. The intervention commences once the infant begins milk intake during the early OMIs. Additionally, in the late OMIs group, the intervention will initiate 48 h after discontinuing nasal continuous positive airway pressure.

**Discussion:**

OMIs encompass non-nutritive sucking and artificial oral stimulation techniques. These techniques target the lips, jaw, muscles, or tongue of premature infants, aiming to facilitate the shift from tube feeding to oral feeding. The primary objective is to determine the ideal intervention timing that fosters the development of oral feeding skills and ensures a seamless transition from parenteral or nasal feeding to full oral feeding among preterm infants. Furthermore, this study might yield insights into the long-term effects of OMIs on the growth and neurodevelopmental outcomes of preterm infants. Such insights could bear substantial significance for the quality of survival among preterm infants and the societal burden imposed by preterm birth.

**Trial registration:**

chictr.org.cn ChiCTR2300076721. Registered on October 17, 2023.

## Introduction

### Background and rationale {6a}

According to the latest data published by Lancet, the global scene records approximately 13.4 million premature births annually, with the incidence rates varying from 6.8 to 16.2% across 103 countries [1]. Within this context, China accounts for 753,000 of these preterm infants, ranking it as the fourth highest in the world in terms of the number of infants born prematurely [1, 2]. Amid the challenging backdrop of NICUs, one glaring hurdle faced by preterm infants is the acquisition of oral feeding skills, a pivotal facet for their growth, and survival [3, 4]. However, a significant proportion of preterm infants encounter struggles in mastering oral feeding, with an incidence rate reaching up to 40% [5, 6]. This struggle primarily presents issues with sucking, swallowing, and even breathing coordination. These feeding difficulties not only extend hospitalization periods but also impact the quality of life for the infants, placing a significant strain on families and society [5, 6].

Mitigating these feeding challenges, improving oral feeding competencies among preterm infants, and facilitating their seamless shift from parenteral nutrition and nasal feeding to full oral feeding constitute shared concerns and hurdles for NICU healthcare professionals. At the crux of this challenge may lie early oral motor interventions (OMIs), presenting a potential solution. Recent studies reveal that OMIs can improve the oral motor function and oral feeding performance of preterm infants.

The concept of OMIs, as first introduced by the American scholars Fucile et al., encompasses interventions that involve non-nutritive sucking, manual oral stimulation, and similar techniques targeting the lips, jaw, tongue, and muscles of preterm infants [7, 8]. The aim is to aid their transition from nasal to oral feeding. A pivotal study by Arora et al. utilizing the Premature Infant Oral Motor Intervention (PIOMI) as pre-feeding stimulation showed that preterm infant undergoing PIOMI achieved full independent spoon-feeding more rapidly, exhibited greater weight gain, and had lower rates of oral aversion than those in the control group [9].

Additional support for the efficacy of OMIs comes from Aguilar-Rodríguez et al.,  who found that such interventions accelerate the progression to full oral feeding and shorten hospital stays [10]. Systematic and meta-analysis reinforce this conclusion, establishing OMIs as an efficacious strategy for bolstering oral feeding in preterm infants [11–14]. Lv et al.’s work underscores the positive effect of early motor interventions on oral feeding ability of preterm infants [15]. Similarly, Wu et al. concluded that oral massage not only improves sucking efficiency but also diminishes the risk of adverse events such as infections and apnea [16]. Wang et al. further validate that OMIs improved feeding performance in preterm infants and did not increase the occurrence of complications associated with prematurity [17]. Thus, integrating OMIs in NICU presents several significant clinical benefits, including: (1) improving oral feeding skills and reducing the transition period from tube feeding or parenteral nutrition to full oral feeding, thereby increasing feeding efficiency; (2) improving the quality of survival by reducing hospitalization durations; and (3) providing early sensory stimulation to support neurobehavioral development in preterm infants.

Despite these advancements, establishing a standardized timing for initiating OMIs remains elusive. Diverse studies advocate different start times, ranging from the infant’s first day following admission [17] to 48 h after ceasing non-invasive ventilation [18, 19], or at the onset of feeding [15]. The cumulative effects of these divergent starting points remain nebulous, compounded by the lack of long-term follow-up research that would elucidate their extended impacts. Consequently, the primary objective of this study is to compare the effects of different initiation times for OMIs on the feeding progress among preterm infants. Simultaneously, it endeavors to evaluate the long-term outcomes of OMIs on both feeding efficiency and neurodevelopment outcomes in preterm infants.

## Objectives {7}

(i)Feeding outcomes: To determine the influence of differing initiation times of OMIs on feeding outcomes among preterm infants.(ii)Long-term growth and development: To examine the effects of OMIs with varying initiation times on extended growth and development trajectory of preterm infants.(iii)Neurodevelopmental outcomes: To explore the effects of OMIs with different initiation times on neurodevelopmental outcomes in preterm infants.

## Trial design {8}

This study employs a single-blind, randomized, and controlled trial design, assigning preterm infants to one of two groups: early OMIs or late OMIs. The flow chart is presented in Fig. 1.

**Fig. 1 Fig1:**
[figure not shown]
flow chart

## Methods: participants, interventions, and outcomes

### Study setting {9}

This research will take place at the NICU which is a 307-bed tertiary-level referral unit of the West China Second University Hospital, Sichuan University, Chengdu, Sichuan Province, China. This study will be performed during the period from October 20, 2023, to October 20, 2025.

### Eligibility criteria {10}

Inclusion criteriaDiagnosis as preterm, with a birth weight of less than 2500 g, and gestational age ranging from 29^+0^ to 34^+6^ weeks.Stability of vital signs.Absence of major congenital anomalies, such as congenital heart disease, or congenital digestive tract malformations.Requirement non-invasive ventilation support, including the use of a high-flow nasal cannula.Enrollment within the first 72 h of life.

Exclusion criteriaRequirement of mechanical ventilation.Severe asphyxia.Prior enrollment in other studies.Diagnosis of necrotizing enterocolitis (NEC).Diagnosis of periventricular leukomalacia (PVL).Diagnosis of intracranial hemorrhage grade III or higher.Need for reinitiation of non-invasive ventilation support after the start of the OMIs.

There are termination criteria and they are as follows: (1) Occurrence of severe adverse events and complications during the trial. (2) Withdrawal of consent by the parents of the subject. Patients who enter the trial but fail to complete it due to any reason will be considered dropout cases. This includes cases where the doctor determines that the subject has withdrawn from the trial, as well as cases where the subject withdraws on their own, regardless of the timing or reason for withdrawal. All data on the infants will still be recorded.

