##### Early OMIs group

On the basis of routine care, we will implement an oral motor intervention program developed by American researcher Fucile, adapted for the Chinese context made by the domestic expert, Lv et al. [7, 15]. The program includes oral stimulation, which involves stimulation of the lips, cheeks, gums, and tongue, along with non-nutritive sucking. The intervention will start once the infant begins to receive milk and exhibits stable vital signs. It will be conducted once a day, for 15 min at a time, and will continue until the infant reaches full oral feeding and maintains it for 48 h without the need for tube feeding. The timing of each intervention is set for 15–30 min before any feeding session, within the hour of 8:00–18:00. All interventions will be performed by charge nurses who have received uniform training. If the infant experiences changes in their condition such as decreased oxygen saturation, bradycardia, or asphyxia, the intervention will be stopped.

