##### Late OMIs group

The interventions for OMIs will be initiated 48 h following the discontinuation of nasal continuous positive airway pressure. The early OMIs group and the late OMIs are the same in every aspect, with the sole distinction being the difference in the start time.

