#### Sample size {14}

The sample size was calculated using the online calculator available at http://powerandsamplesize.com/, based on the primary outcome measure of transition time—the duration time from the initiation of feeding to achieving full oral feeding. A two-sample independent means comparison method was applied for this calculation. The sample size calculation accounts are based on a type I error probability of 5% and a statistical power of 80%. According to our pilot study (*n* = 26), the mean transition times for the two groups were found to be μ1 = 11.36 days for the early OMIs group, μ2 = 13.40 days for the late OMIs group, with a *σ* = 4.99 days. The two groups were allocated in a 1:1 ratio; the initial calculation indicated a need for 126 participants per group. To account for potential dropouts or exclusions, the sample size was augmented by 10%, resulting in a total of 280 participants, or 140 participants per group.

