### Implementation {16c}

After obtaining consent and before proceeding with the medically necessary procedure, the research nurse will perform randomization of the preterm to determine the allocation of the study intervention.

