## Statistical methods

### Statistical methods for primary and secondary outcomes {20a}

The intention-to-treat analysis (ITT) will be the main analysis, with a per-protocol set (PPs) analysis conducted simultaneously. A significance level of *P* < 0.05 will be considered statistically significant. In the ITT analysis, all subjects will be included in the group to which they are assigned, regardless of whether they completely received the intervention. (1) Descriptive statistics will be used to summarize baseline characteristics. Continuous variables will be presented as Mean ± Standard deviation and categorical variables as percentages (%). (2) For comparisons between groups, Student *t*-tests will be applied for continuous variables, and chi-square tests will be utilized for categorical variables. (3) Assessment of efficacy: for continuous variables, independent Student *t*-tests will be employed for evaluation if conditions are met. (4) For data that do not follow a normal distribution, ordinal data, or data with significantly unequal variances, non-parametric tests will be used. The statistical analysis will be conducted using the medical statistical software SPSS 23.0 (SPSS, IBM Corporation, Armonk, NY, USA).

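### An exclusion criterion that can only be met after randomisation has a window that opens at a different time in each arm; applied as written, it conflicts with ITT and could favour early OMIs

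*Protocol article*

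**What the plan says.** Eligibility criteria {10} place this item among the exclusions: "Need for reinitiation of non-invasive ventilation support after the start of the OMIs". The same section requires non-invasive support at entry and "Enrollment within the first 72 h of life". Under Implementation {16c}, after consent and before the study procedure, "the research nurse will perform randomization of the preterm to determine the allocation of the study intervention".

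The arms differ only in when OMIs begin. For the early group, "The intervention will start once the infant begins to receive milk and exhibits stable vital signs"; being off respiratory support is not required. For the late group, "The interventions for OMIs will be initiated 48 h following the discontinuation of nasal continuous positive airway pressure". The late-group section describes the two programmes as otherwise identical, "with the sole distinction being the difference in the start time".

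The main analysis under {20a} is ITT, in which "all subjects will be included in the group to which they are assigned, regardless of whether they completely received the intervention". Sample size {14} adds an allowance: "To account for potential dropouts or exclusions, the sample size was augmented by 10" per cent. The eligibility section classes infants who do not complete the trial as dropouts and says their data continue to be recorded. It does not say whether infants who meet the restart criterion stay in the analysis.

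**The concern.** An eligibility criterion should be decidable before allocation. This one is not: no infant has started OMIs when randomised, so the item can only act as a rule for removing infants afterwards.

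The removal window also depends on the arm, because it opens at OMI start, which is exactly what the trial randomises. Consider two similar infants who stop CPAP and need support again 24 h later. The early-arm infant, if already on milk and OMIs, meets the exclusion. The late-arm infant has not begun OMIs and does not.

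If infants who restart support take longer to reach full oral feeding, removing more of them from the early arm would lower that arm's mean transition time with no treatment effect. That is selection bias in the primary outcome, in the direction of the pilot result.

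**Working it through.** **1. Order of events.** Enrolment within 72 h of life on non-invasive support → randomisation → OMI start (arm-specific) → possible restart of support. The criterion refers to the last step, so it always follows allocation.

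**2. Windows side by side.**

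| Timing of restart | Early arm (OMIs begun at first milk) | Late arm (OMIs begin 48 h after stopping nasal CPAP) |
|---|---|---|
| After first milk, up to 48 h off CPAP | Excluded | Not excluded |
| After late-arm OMIs have begun | Excluded | Excluded |

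Wherever milk starts before 48 h off CPAP, the late-arm window lies inside the early-arm window. Exclusions should then be at least as frequent in the early arm.

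**3. The plan's own figures.** From Sample size {14}: means 11.36 and 13.40 days (difference 2.04), SD 4.99, 140 randomised per arm. With n = 2(z₀.₉₇₅ + z_power)² × SD²/difference², 80% power gives 94 per group and 90% power gives 126. The stated 126 therefore matches 90% power, not the stated 80%; 126/0.9 = 140 is correct. This is a separate discrepancy and does not bear on the present point.

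**4. Illustrative size if excluded infants leave the analysis.** None of the next three inputs is in the protocol; all are assumptions.

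- r = share of infants who restart support after first milk
- f = share of those restarts falling within 48 h of stopping CPAP
- k = extra days to full oral feeding in infants who restart

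The early arm loses r; the late arm loses r(1 − f). With no true effect, the early analysed mean is that of infants who do not restart. The late analysed group still contains a share rf/(1 − r(1 − f)) of infants who restart. Hence:

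spurious difference = k·r·f / (1 − r(1 − f)), in favour of early OMIs

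SE = 4.99 × √(1/n_E + 1/n_L), with n_E = 140(1 − r) and n_L = 140(1 − r(1 − f)). Type I error is P(|Z + difference/SE| > 1.96).

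- **r = 0.20, f = 0.6, k = 5:** difference = 0.60/0.92 = 0.65 days (0.65/2.04 = 32% of the planned effect). n_E = 112, n_L ≈ 129, SE = 0.645, type I error about 17%.
- **r = 0.10, f = 0.6, k = 5:** difference = 0.30/0.96 = 0.31 days. n_E = 126, n_L ≈ 134, SE = 0.619, type I error about 8%.
- **Total loss from this rule held at 10% across both arms, f = 0.6, k = 5:** r(1 + 0.4)/2 = 0.10, so r = 0.143. Difference = 0.45 days, type I error about 11%.
- **Range over r = 10–30%, f = 40–80%, k = 3–8 days:** 0.13 to 2.04 days, type I error 5.5% to 87%. The upper end needs all three extremes at once.

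If every randomised infant is kept, the difference from this source is zero.

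**The case against.** The strongest reply is that the protocol never says these infants leave the primary analysis. {20a} puts every subject in the assigned group, and the eligibility section keeps recording data on non-completers. Read together, an infant who restarts support may stop OMIs or leave the per-protocol set and still be counted under ITT. On that reading the rule causes no selection bias in the main analysis. This stands as a possible reading, but the protocol does not state it, and the item is filed as an exclusion criterion.

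A reader might infer from the sample-size wording that these infants are expected to be dropped. The text does not support that: the 10% covers dropouts and exclusions of every kind.

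The late-arm window is also less certain than the table suggests. The late-group section counts from stopping nasal CPAP, while t2 in the Table 2 key counts from stopping non-invasive ventilation, and eligibility treats high-flow cannula as non-invasive support. A late-arm infant might therefore begin OMIs while on high-flow. That milk starts before weaning in most early-arm infants is plausible but not documented. A late-arm infant who restarts within 48 h might also restart again after OMIs begin and then be excluded, which would reduce the imbalance.

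Finally, a reader might extend the criticism to the NEC, PVL, haemorrhage and mechanical-ventilation exclusions. Nothing in the protocol shows that those are applied after randomisation, so the point is confined to the restart item.

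**Conclusion.** The criterion is wrong as written. It is a post-randomisation event listed as eligibility, its window depends on the allocated arm, and removing infants under it contradicts the stated ITT rule. This follows from the text alone.

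Bias in the primary outcome is conditional. It requires that infants meeting the criterion are actually left out of the analysis, that more of them are in the early arm, and that they reach full oral feeding later. A reader might conclude that the trial will be biased towards early OMIs, or by a particular amount. The documents support neither, because they leave the handling of these infants open and give no restart rate, timing or excess days. Differences of about 0.31 to 0.65 days, with type I error of about 8% to 17%, show what moderate assumptions would imply; they are not estimates for this trial.

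**What to change.** Take the restart item out of the eligibility criteria. Reconcile Eligibility criteria {10}, Sample size {14} and Statistical methods {20a} by stating that every randomised infant stays in the ITT primary analysis and is followed to full oral feeding, whatever happens to respiratory support. Record restart of non-invasive support as a post-randomisation event and report it by arm. Use it at most to define a per-protocol or sensitivity set.

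Whether OMIs should stop after a restart is a clinical matter and is not judged here.

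The cost is one wording amendment. Infants already set aside can be returned to the analysis, since the protocol says their data continue to be recorded. The small downside is a slightly diluted ITT effect.

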### Who will take informed consent? {26a}

The coordinating center will aid in obtaining consent for the research team to approach individuals who may qualify for participation. An eligible status will be determined by a research nurse, and she will also provide information about the study and ensure that signed informed consent is obtained.

### Additional consent provisions for collection and use of participant data and biological specimens {26b}

N/A: There will be no collection of biological specimens as part of this trial.

### Interventions

#### Explanation for the choice of comparators {6b}

The studies demonstrate that oral motor intervention conducted after discontinuing non-invasive ventilation for 48 h is effective [18, 19].

#### Intervention description {11a}

The specific intervention plan is shown in Table 1.

**Table 1 Tab1:** Oral stimulation program [7]

Structure	Stimulation steps	Purpose	Frequency	Duration
Cheek	1. Place index finger at the base of the nose 2. Compress the tissue, move finger toward the ear, then down and toward the corner of the lip (i.e., C pattern) 3. Repeat for other side	Improve range of motion and strength of cheeks and improve lip seal	4 $$\times$$ each cheek	2 min
Upper lip	1. Place index finger at the corner of the upper lip 2. Compress the tissue 3. Move the finger away in a circular motion, from the corner toward the center and to the other corner 4. Reverse direction	Improve lip range of motion and seal	4 $$\times$$	1 min
Lower lip	1. Place index finger at the corner of lower lip 2. Compress the tissue 3. Move the finger away in a circular motion, from the corner toward the center and to the other corner 4. Reverse direction	Improve lip range of motion and seal	4 $$\times$$	1 min
Upper and lower lip curl	1. Place index finger at center of lip 2. Apply sustained pressure, stretch downward toward the midline 3. Repeat for lower lip—apply sustained pressure, and stretch upward toward the midline	Improve lip strength, range of motion and seal	2 $$\times$$ each lip	1 min
Upper gum	1. Place finger at the center of the gum, with firm sustained pressure, slowly move toward the back of the mouth 2. Return to the center of the mouth 3. Repeat for opposite side	Improve range of motion of tongue, stimulate swallow, and improve suck	2 $$\times$$	1 min
Lower gum	1. Place finger at the center of the gum, with firm sustained pressure slowly move toward the back of the mouth 2. Return to the center of the mouth 3. Repeat for opposite side	Improve range of motion of tongue, stimulate swallow, and improve suck	2 $$\times$$	1 min
Internal cheek	1. Place finger at inner corner of lips 2. Compress the tissue, move back toward the molars, and return to corner of lip 3. Repeat for other side	Improve cheek range of motion and lip seal	2 $$\times$$	2 min
Lateral borders of the tongue	1. Place finger at the level of the molar between the side blade of the tongue and the lower gum 2. Move the finger toward midline, pushing the tongue towards the opposite direction 3. Immediately move the finger all the way into the cheek, stretching it	Improve tongue range of motion and strength	2 $$\times$$	1 min
Midblade of the tongue	1. Place index at the center of the mouth 2. Give sustained pressure into the hard palate for 3 s 3. Move the finger down to contact the center blade of the tongue 4. Displace the tongue downward with a firm pressure 5. Immediately move the finger to contact the center of the mouth at the hard palate	Improve tongue range of motion and strength, stimulate swallow, and improve suck	4 $$\times$$	1 min
Elicit a suck	1. Place finger at the midline, center of the palate, and gently stroke the palate to elicit a suck	Improve suck and soft palate activation	N/A	1 min
Pacifier	1. Place pacifier in mouth	Improve suck and soft palate activation	N/A	3 min

